## The LIAM Mc Trial

Review of previous imaging assessing the location, type of, history and progression of bone metastases will be defined at the outset.

Bone pain details at rest, ADL's and with physical activity will be recorded.

Incidence and severity of any adverse event and skeletal complications related to and unrelated to exercise will be recorded throughout the programme.

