### 6.1 Sample size justification

Parallel Sampling Groups will be used from Q3 of Year 1 on (after completion of the 6 participant Initial Phase). A new group of 6 participants will commence the programme every 6 weeks, in order to facilitate workload and resource management (see Figure 2, Section 3.2.1). This will mean two groups are at two different timepoints in the programme at any given date. 12 groups of 6 men each are planned in total, including the pilot phase group, with a total anticipated accrual of 72 participants over two years.

Given that the main objectives of this study are to evaluate the *feasibility* of introducing a men's malignancy survivorship programme, we have not calculated the sample size that would be required to reliably estimate the effect of the programme on patient outcomes. This follows from established best practices in pilot and feasibility studies [19] for which there is usually too much uncertainty in the various factors that are needed to make a sample size calculation robust (e.g. effect sizes of interest, outcome variability, etc.). Our sample size justification is instead based on trying to recruit the largest possible sample given existing financial and pragmatic constraints. This will allow us to maximize our ability to identify barriers to implementation, as well as the information that will be required to properly design any subsequent trials of the programme's efficacy (e.g. robust estimation of estimator variability, even for binary outcomes [20]). At the same time, the potential costs of over-recruitment are largely absent for this study. Most importantly, there are no excess risks to patients receiving the intervention, and all patients are guaranteed access to the current standard of care. Further, most of the financial costs of the study are fixed, regardless of the actual number of patients recruited into the study.

Given that the goal of a feasibility study is to identify problems that would impede the conduct of a larger, efficacy study, we have set the sample size at 60 based on advice from Viechtbauer et al. [21], which is aimed at being able to detect failures in study processes that would occur just 5% of the time (with 95% confidence). A sample size of 72 allows for sample attrition from men withdrawing, illness, or waning commitment as commented.

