### 7.1 Recording of Adverse Events

Adverse events (AE) of interest (those deemed potentially related to the intervention) will be recorded and assessed for relationship to the intervention programme throughout the study period. Adverse Events will be documented and graded in accordance with Common Terminology Criteria for Adverse Events (CTCAE) v5.0. Patient reporting of an adverse event to an HCP will trigger recording of the AE, these will not be assessed routinely at every visit due to resources.

Serious Adverse Events (SAE's), defined for the purposes of this study as CTCAE v5.0 grade  $\geq 3$  adverse events of any kind, or those grade  $< 3$  but deemed by an investigator to be serious, will be reported to the LIAM Mc Steering Group for review at the following meeting. SAE's of grade  $\geq 4$  will trigger a pause in the study for safety reasons until the AE has been formally assessed by the Steering Group and a decision made to either proceed with or terminate the study.

We do not anticipate any adverse events associated with completion of the patient reported outcomes. Patients will have the option of skipping questions they do not wish to answer. In event that study participation does result in any event that has significant negative consequences for the subject, this will be recorded by an investigator in the EDC (Electronic Data Capture) and will be reported to the Sponsor and Ethics committee.

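### Section 7.1 contradicts itself, and Section 4.4.3.1, on which adverse events are recorded and which can pause the study

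*Protocol*

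**What the plan says.** Three statements in the protocol define the scope of adverse event handling.

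- **Section 7.1, first paragraph (recording).** "Adverse events (AE) of interest (those deemed potentially related to the intervention) will be recorded and assessed for relationship to the intervention programme". This holds for as long as the study runs. Capture is passive: "Patient reporting of an adverse event to an HCP will trigger recording of the AE", with no routine enquiry at each visit.
- **Section 7.1, second paragraph (serious events and pause).** Serious events are those of CTCAE v5.0 grade 3 or higher, "adverse events of any kind, or those grade" below 3 that an investigator considers serious. They go to the Steering Group. A serious event of grade 4 or higher "will trigger a pause in the study for safety reasons until the AE has been formally assessed by the Steering Group", followed by "a decision made to either proceed with or terminate the study". Neither the definition nor the trigger mentions cause.
- **Section 4.4.3.1, Safety and tolerability Assessment.** "Incidence and severity of any adverse event and skeletal complications related to and unrelated to exercise will be recorded throughout the programme".

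The study plans 12 groups of 6 men, "with a total anticipated accrual of 72 participants over two years" (Section 6.1). Follow-up runs to 6 months after the 12-week programme (Section 4.4.9).

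**The concern.** The three statements give three different sets of events. The pause is the strongest safety action in the protocol, and the set of events that can set it off is not fixed.

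Take a man with metastatic disease who has a grade 4 complication of his systemic therapy, or who dies of his cancer (grade 5 on the CTCAE scale that Section 7.1 adopts). Under the second paragraph of 7.1 the study stops for everyone until the Steering Group has met. Under the first paragraph the event is not of interest, so it is neither recorded nor assessed for relationship. Under Section 4.4.3.1 it is recorded if it falls during the programme. Two teams could follow the protocol faithfully and act in opposite ways.

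Two things are at stake. One is whether the study is halted by events that the programme did not cause. The other is the meaning of the safety record: a table limited to events judged related cannot be read as an all-cause table, and a count of pauses cannot be read as a count of programme harms.

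**Working it through.** **Step 1. The passages side by side**, for a grade 4-5 event that is clearly due to disease or drug therapy:

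| Place | Recorded? | Assessed for relationship? | Pauses the study? |
|---|---|---|---|
| 7.1, first paragraph | No | No | Not addressed |
| 7.1, second paragraph, read literally | Yes, reported to the Steering Group | Not stated as a condition | Yes |
| 4.4.3.1, Safety and tolerability Assessment | Yes, during the programme | Not addressed | Not addressed |

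The rows cannot all be followed for the same event.

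**Step 2. The plan's own arithmetic.** The protocol gives no background event rate and no probability of a pause. The nearest stated figure is the target of 60 in Section 6.1, set to see a process failure of 5% frequency with 95% confidence:

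n = ln(1 - 0.95) / ln(1 - 0.05) = 58.4, rounded up to 59.

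The stated 60 agrees to within one man; at n = 60 the probability is 1 - 0.95^60 = 95.4%. The planned accrual is 12 x 6 = 72.

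**Step 3. The same formula applied to the pause, read literally.** Let p be a man's probability, over his time in the study, of a reported grade 4-5 event not caused by the programme. With independent men:

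P(at least one pause) = 1 - (1 - p)^72; expected number of men with such an event = 72p.

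| p (assumed) | P(at least one), 72 men | Expected men, of 72 | P(at least one), 60 men |
|---|---|---|---|
| 0.5% | 30% | 0.36 | 26% |
| 1% | 52% | 0.72 | 45% |
| 2% | 77% | 1.44 | 70% |
| 3% | 89% | 2.16 | 84% |
| 5% | 97.5% | 3.6 | 95% |

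For 72 men the probability reaches one half at p = 1 - 0.5^(1/72) = 0.96%.

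Passive capture lowers the effective p. If, for illustration, half of such events came to the team's notice, a true 2% would act as 1%, and the chance would fall from 77% to 52%.

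**Step 4. The narrow reading.** If only events judged potentially related can trigger, a harmless programme with perfect attribution never pauses the study. If 10% of background events were wrongly judged related (again an assumption), p = 5% becomes 0.5% and the chance is 30%. At p = 5% the choice of reading alone therefore moves the chance of a pause from 97.5% to somewhere between 0% and 30%.

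**Step 5. What a pause says about harm, on the literal reading.** Suppose the programme truly adds a 5% risk, so that the combined risk is 1 - (1 - p)(1 - 0.05). At p = 5% the chance of a pause moves from 97.5% to 99.9%, so the occurrence of a pause is almost uninformative. At p = 1% it moves from 52% to 99%, which is informative.

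**The case against.** **A pause with committee review is a legitimate cautious choice.** This is a small uncontrolled study that exercises men with bone metastases, and a trigger that errs towards stopping costs mainly time. That stands. The criticism is not that the rule is too cautious but that its scope is stated in incompatible ways.

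**The literal reading is not the only one.** The opening of 7.1 may be meant to govern the whole section, so that serious events are a subset of the potentially related ones and the words on kind refer to type of event. This also stands as a possible reading. It does not remove the problem: on that reading unrelated grade 4-5 events are not recorded under 7.1 and trigger nothing, which conflicts with Section 4.4.3.1.

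Stronger conclusions that a reader might draw are not supported:

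- *That the pause will very probably fire.* This needs a background rate that the protocol does not give. Below about 1% the chance is one half or less. Eligibility favours recovered or stable men, some without metastases, and capture is passive.
- *That the procedure cannot separate programme harm from disease.* At higher p this is true of the trigger, not of the whole procedure: the Steering Group formally assesses the event before deciding. Nor does the protocol tie that decision to the number of pauses.
- *That Section 4.4.7 contradicts the pause by listing death as a reason for discontinuation.* That list concerns one man's exit, whereas 7.1 sets a study-level action. Both can apply to the same death.
- *That pauses will cost sessions or spoil the participation count.* The protocol gives no pause length and does not say which activities stop. Section 4.3.2 says that all 12 weeks of activities will take place, and Section 4.4.4 already catalogues implementation problems.

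**Conclusion.** The point holds as an inconsistency of scope. The two paragraphs of 7.1 differ on whether cause matters, and Section 4.4.3.1 sides with neither. The same disease-related grade 4-5 event could halt the study or leave no trace in the 7.1 record, depending on which text the team follows.

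Read literally, a harmless programme would be paused at least once with probability 30% to 97.5% for background risks of 0.5% to 5% per man. This range assumes 72 enrolled men, independent events and one common risk of a *reported* event. The risks are illustrations, and the figures show sensitivity to the reading rather than a forecast.

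The descriptive feasibility analysis is not invalidated. What is affected is when the trial stops and what its safety record can be taken to mean.

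**What to change.** Reconcile the two paragraphs of Section 7.1 with each other and with the Safety and tolerability text in Section 4.4.3.1. A single statement should say:

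1. which events are recorded;
2. which of these are assessed for relationship to the programme;
3. which can trigger the pause.

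The choice of rule, and the basis for proceeding or terminating, belong to the sponsor and the Steering Group; none is proposed here.

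Whatever scope is kept, assess relationship for every event that can trigger the pause, and tabulate grade 3 and higher events by that assessment, showing any that were not assessed as such. A pause is then reported next to the judged cause of the event and is not itself read as evidence of programme harm.

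The cost is a wording change in two sections, an ethics notification, and a prompt relationship judgement for each such event. If the wider scope is chosen, that judgement is extra work, because 7.1 now requires it only for events of interest.

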## 8.0 Data Handling and Record Keeping

---

### 8.1 Confidentiality

Pseudoanonymised study data will be maintained in a dedicated CASTOR database in a secure password-protected location on the UCC server network. A unique study ID number will be assigned to each subject. This will be linked to the patient identifying information by a list maintained by the PI in a secure location, separate to other study documentation. This is primarily to facilitate subsequent follow-up of patients. The patient identity list will remain at the clinical site and will not be forwarded to any third party, including the EDC platform. The data will be transported by the delegated team member from the Mardyke Arena to the clinical site (CUH). It will be available for review by the study monitor, auditors or inspectors as required. University College Cork, as study Sponsor, is the data controller for the research database.

### 8.2 Source Documentation

Electronic and/or paper case report form (CRF) will be used as source documentation in this project.

### 8.3 Case Report Forms

Pseudoanonymised data will be entered onto study specific eCRFs. With the EDC platform, almost all actions performed by users are tracked. It is possible to review what each user did in any field. Any missing data will be explained. If a data point cannot be answered due to missing data or other known reason, the EDC platform allows for this to be noted, any item on the CRF left blank because the procedure was not performed will be denoted by “N/D”. Items not applicable to the individual case, will be recorded as “N/A”. All entries should be printed legibly in black ink where paper used. In correcting any error, a single straight line will be drawn through the incorrect entry without obscuring the original entry and the correct entry recorded above it. All such changes must be initialed and dated as per ICH-Good Clinical Practice (GCP).

### 8.4 Records Retention

Study documents and pseudoanonymised data will be kept for 10 years as per UCC Code of Research Conduct (Data Protection Notice v4.1) after the end of the study. Thereafter, the data may be stored for a further period of time for legal reasons (e.g. revised retention obligations), or more if required by law. Study documents will thereafter either be destroyed or fully anonymized and retained, as scientific interests dictate at that time, in line with UCC’s Data Protection Policy and the UCC Code of Research Conduct.

## 9.0 Ethical Considerations

---

This study will be conducted in accordance with the Declaration of Helsinki, the applicable sections of ICH GCP, and the terms of approval of the responsible Ethics Committee, the Clinical Research Ethics Committee (CREC) of Cork Teaching Hospitals. This study was submitted for Full ethical approval by the CREC on October 14th 2022. If any data breach is detected during the study, it will be reported in <72 hours to the Data Protection Commission (DPC).

## 10.0 Study Finances

---

### 10.1 Funding Source:

The costs of this study will be funded by an Irish Cancer Society grant (MHI22BAM) for 2 years for a total of 299,988€ including personnel and non-personnel costs. Additional part-funding for some data analysis and management is available through the HRB UCC Cancer Trials Group (CTIC 2021-02) grant.

Patients will not be paid for taking part in the study. Patients travel costs will be covered to ensure they are not left out of pocket.

## The LIAM Mc Trial

This patient access fund exists to ensure that no man is denied access to the programme or to be involved as a PPI representative for want of travel costs, interpreter costs, or other unforeseen costs. This aims to ensure that men from underserved communities, at geographic distance from the CUH, and those with an unmet need can participate fully in this programme.

### 10.2 Indemnity for the performance of the study

Protocol and prototype indemnity will be provided by UCC. Malpractice indemnity will be provided to research staff as part of Clinical Indemnity Scheme coverage provided by the States Claims Agency.

## 11.0 Sponsorship

---

The study is sponsored by University College Cork (UCC).

## 13.0 Study Documents Versions Log

**IMPORTANT NOTE:** The following documents have their own version and date and have been ethics approved as individual documents.

**Study Title:** The LIAM Mc Trial - Linking In with Advice and supports for Men impacted by Metastatic cancer

**Short Title:** The LIAM Mc Trial   **Study Reference:**   **Sponsor:** University College Cork (UCC)   **UCC code:** 22052

| CREC
REFERENCE: | First ethics approval
Sent:
Approval Date: CREC
rev ref: | Amendment #1                                                                                             | Amendment
#2                   | Amendment #3                                                                                            | Amendment #4                                                   | Amendment #5 |
|--------------------|-------------------------------------------------------------------|----------------------------------------------------------------------------------------------------------|-----------------------------------|---------------------------------------------------------------------------------------------------------|----------------------------------------------------------------|--------------|
| Protocol           | 24-Nov-22                                                         | Physio CRF,
amend definition
of exercises and
time taken.
Added Bi-weekly
data collection | Change
to
Dietician
CRF, | Addition to
Dietician CRF,
individual
patient
assessment
document and
data collection | Nurse CRF and
CNS CRF change
due to change of PI
name |              |
